### Randomisation and blinding

In the present RCT, PS patients will enter the trial sequentially, and their covariates (sex, age, BMI) will be used to adapt the randomisation process. A covariate-adaptive randomisation procedure for two treatments will be applied to balance the treatment allocations across the selected covariates (sex, age, BMI) using R software. The randomisation procedure will be conducted by a biostatistician who is not directly involved in the study. At the allocation visit, PS patients, who are randomly allocated to either the prebiotic or placebo group, will obtain a package of sachets containing the supplement (prebiotic or placebo) from a researcher not directly involved in the study. The trial employs a double-blind design, in which the researchers (excluding the one responsible for supplement distribution), laboratory personnel, and participants are unaware of which subjects receive the prebiotic and which the placebo.

### Intervention

In this RCT, the nutritional intervention will last 8 weeks. During the first week, participants in the study group will be instructed to consume only one sachet of the supplement daily with breakfast to minimise potential side effects. From week 2 until the end of the intervention, participants will consume two sachets daily (at breakfast and dinner), amounting to a total dose of 15 g of supplement (prebiotic or placebo) each day. Participants will be instructed to dissolve the sachet content in water or juice and consume it 15–20 min before a meal. The PS participants will receive questionnaires on compliance and adverse reactions, and will be asked to record their supplement intake, any adverse reactions (gastrointestinal and other), and medication use during the study. The dosage of the supplement and the duration of the intervention were based on previous studies involving adults [28]. Participants from the control group (healthy individuals) will not be the object of any supplementation.

### Study outcomes

The primary outcome is the between-group difference in the change in PASI score from baseline (T0) to the close-up visit (T1) after the 8-week intervention, which will inform about the change in the severity of skin lesions. The secondary outcomes are changes within and between the prebiotic and placebo group after the 8-week intervention in:

selected clinical parameters,BMI and body composition,nutritional status,resting metabolic rate and respiratory quotient,quality of life,faecal microbiota abundance and diversity,faecal SCFA profile and concentration,level of blood inflammatory cytokines.expression of genes of inflammatory response in skin,level of blood and faecal biomarkers of intestinal barrier permeability;concentration of urine and faecal volatile organic compounds (VOCs).oxidative stress parameters.

### Timeline of the study

An overview of the study design, including the timeline of participant visits, assessment point times, and examined variables, is given using the SPIRIT diagram (Table 2) and Figs. 1 and 2.

Three sample collection points for each PS participant are planned: at enrolment (-T_1_), baseline (T_0_) and at close-up visit (T_1_), after the 8-week nutritional intervention, and two sample collection points for each healthy participant: at enrolment (-T1) and baseline (T_0_) (Table 2). Check-up visits will be carried out in the Dermatology Clinic of the Municipal Hospital in Olsztyn under the supervision of dermatologists.

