## Methods

### Study design

A single-centre, randomised, placebo-controlled, double-blind clinical trial with parallel arms and equal allocation is proposed. Additionally, a control group of healthy subjects will be established. The study adheres to the Consolidated Standards of Reporting Trials (CONSORT) 2010 [23] and Standard Protocol Items: Recommendations for Interventional Trials (SPIRIT) 2013 Statements [24] (Related file). The trial has been registered at ClinicalTrials.gov (NCT05971992) on August 1, 2023.

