**Fig. 1 Fig1:**
[figure not shown]
Flow diagram of participant recruitment according to CONSORT [23]

Healthy individuals will be invited to participate in the study voluntarily through an advertisement posted on the Institute of Animal Reproduction and Food Science of the Polish Academy of Sciences (IAR&FR PAS) website (www.pan.olsztyn.pl). Individuals interested in the study will be scheduled for the enrolment visit at the Dermatology Clinic to sign the informed consent form. They will undergo the eligibility assessment (Table 1). Ultimately, healthy subjects who meet the inclusion and exclusion criteria will be enrolled in the control group (Fig. 1).

**Table 1 Tab1:** Criteria for inclusion and exclusion

Study group	Control group
Inclusion Criteria	Inclusion Criteria
• Age 18–65 years old • Mild psoriasis (PASI < 10) • Body mass index (BMI) < 30 kg/m^2^ • Omnivorous diet, • Negative tTG-IgA, • Willingness to give informed consent	• Age 18–65 years old • Good health • Body mass index (BMI) < 30 kg/m^2^ • Omnivorous diet, • Negative tTG-IgA, • Willingness to give informed consent
Exclusion Criteria	Exclusion Criteria
• Chronic or acute inflammatory disease (other than psoriasis), in particular diabetes, gastrointestinal disease, cardiovascular complications, heart, kidney and liver failure, thyroid disease, cancer • Current anti-psoriatic treatment (systemic or biologic) • Antibiotics within 14 days before sampling • Probiotic, prebiotic, and/or synbiotic supplements intake within 4 weeks before sampling • Pregnancy, breastfeeding • Surgery within 6 months before sampling	• Chronic or acute diseases, in particular, skin disease, diabetes, gastrointestinal disease, cardiovascular complications, heart, kidney and liver failure, thyroid disease, cancer • Antibiotics within 14 days before sampling. • Probiotic, prebiotic, and/or synbiotic supplements intake within 4 weeks before sampling • Pregnancy, breastfeeding • Surgery within 6 months before sampling

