**Table 2 Tab2:**
[figure not shown]
Schedule of enrolment, intervention and assessments [24]

During the enrolment visit (-T_1_), vitals (systolic, diastolic and pulse pressure), body height (stadiometer Seca 213, Seca GmbH & Co, Hamburg, Germany), and body weight (balance Seca 813 Med, Seca GMBH & Co, Hamburg, Germany) were measured in all participants. The body mass index (BMI) was calculated as a ratio of body mass to the square of body height and expressed in kg/m^2^. In addition, a qualified nurse collected a sample (8 mL) of venous blood into a serum vacuum tube (Greiner Bio-One GmbH, Kremsmünster, Austria) to perform a serum IgA antibody against tissue transglutaminase (anti-tTG IgA) assay to rule out gluten-related diseases (e.g., celiac disease) [30]. A dermatologist assessed the severity of skin lesions in PS patients using the Psoriasis Area and Severity Index (PASI).

During the check-up visits T_0_ and T_1_, vitals, anthropometric indices, and body composition will be measured, and an oral glucose tolerance test and metabolic rate evaluation will be performed in all participants after an overnight fast. Additionally, surveys on nutritional status and quality of life will be conducted, and samples of biological materials (blood, urine, urine after SAT, stool, skin) will be collected.

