### Multi-sugar absorption test

Before the check-up visits T_0_ and T_1_, all participants will complete the multi-sugar absorption test (SAT) [31]. They will be instructed to perform the test on a day off from work, one day before the scheduled check-up visits. Participants will be asked to follow pre-test restrictions: maintaining normal daily activities and typical dietary patterns, but 2 days before the test, avoiding consumption of sugars (sucrose, lactulose, sucralose, erythritol and rhamnose) present in the sugar mixture, as well as alcohol, caffeine, and spicy foods.

On the test day, after an overnight fast and morning bladder emptying, subjects will ingest a sugar mixture (containing 1 g sucrose (PA-01-0238-O, POL-AURA, Morąg, Poland), 1 g lactulose (PA-03-9831-C, POL-AURA, Poland), 1 g sucralose (PA-03-9213-C, POL-AURA, Poland), 1 g erythritol (E968, Hortimex Plus Sp. z o.o. Sp. K,. Konin, Poland) and 0.5 g L-rhamnose (PA-03-1712-C, POL-AURA, Poland)), freshly dissolved in 150 mL of tap water. They will then be instructed to collect urine in a tulip-type container over 12 h. During the test, they will be permitted to drink water (150–200 mL per hour) to maintain adequate urinary output, but will not be allowed to eat for the first 5 h. Participants will collect urine samples at three intervals: 2, 5, and 12 h after ingesting the sugar mixture, and record the urine volume at each interval.

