Statistical analyses and visualisations will be performed using the R software (www.r-project.org), Statistica 14 software (StatSoft, USA) or GraphPad Prism version 10.0.3 (275) for Windows, GraphPad Software, LLC (Boston, MA, USA). The data within groups will be tested for normality using the Shapiro–Wilk test. Levene’s test will be performed to assess the homogeneity of variances within groups. For secondary outcomes and cross-sectional comparisons, two- or three-group comparisons will be performed using a t-test or ANOVA; if assumptions are not met, alternative nonparametric tests will be conducted (Mann–Whitney or Kruskal–Wallis test). Results will be considered statistically significant when *p* < 0.05. Correlations between selected parameters will be tested using Pearson or Spearman correlation, with prior tests for heteroscedasticity. Logistic and linear regression will be used to estimate associations between parameters. Missing data will be summarised by group with reasons; sensitivity analyses will assess robustness to missingness. Baseline total energy intake and baseline habitual dietary fibre intake from foods (excluding the allocated supplement) will be considered in prespecified sensitivity analyses (and in microbiome association models where relevant) to account for background diet; total fibre intake including the study supplement will not be included as a covariate in the primary efficacy model. For high-dimensional outcomes (e.g., microbiome taxa, metabolomics/VOCs), false discovery rate (Benjamini–Hochberg) control will be applied.

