The protocol and the aims of our RCT were developed by an interdisciplinary research team. Well-trained researchers will follow all rigorous procedures established for this RCT to ensure that the research is conducted according to standards of best practice. Another strength of this RCT is that it is a prospective study with a comparable healthy subject control group. We expect that the wide spectrum of results obtained will provide new insights into the impact of ITFs on the range of physiological, functional, and health-related parameters, from changes in gut microbiota characteristics and intestinal barrier function to health-related and metabolic biomarkers of the gut-skin axis. This research may elucidate the nature of the interaction between gut microbiota and skin, providing further insights into the functioning of the gut-skin axis. Given the important physiological role of gut microbiota, our study will be a pioneer in assessing the efficacy of ITFs in restoring gut homeostasis in individuals with PS and will also determine whether ITF-induced microbiota modulation is an effective method for alleviating inflammation and reducing the severity of PS-related skin lesions. We anticipate that the findings from our study will enable the development of personalised dietary therapies involving ITFs, which would avoid the side effects associated with other conventional psoriasis treatments. It is worth emphasising that the proposed prebiotic intervention approach is safe, relatively straightforward to implement, and could enhance current management strategies for this dermatosis. Ultimately, we aim for our research to support a nutritional therapeutic approach for regulating systemic immunity by manipulating the gut microbiota. Specifically, we seek to stimulate the growth and activity of beneficial pro-health bacteria. We believe that such dietary modifications may help reduce the metabolic disorders commonly associated with the development of psoriasis.

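### Comparisons with the non-randomised healthy group are planned with unadjusted tests and so are open to confounding by age, sex and BMI, and the text disagrees on whether that group has a T1 visit

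*Protocol article*

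**What the plan says.** **Who the healthy subjects are.** Study design adds them to a two-arm randomised trial: "Additionally, a control group of healthy subjects will be established". Under Participants, psoriasis patients come from a hospital dermatology clinic and are invited by phone. For the other group, "Healthy individuals will be invited to participate in the study voluntarily through an advertisement posted on the Institute of Animal Reproduction and Food Science". Table 1 gives both groups the same age range (18–65), BMI limit (<30 kg/m²), omnivorous diet, tTG-IgA requirement, and antibiotic, supplement, pregnancy and surgery exclusions. No matching is described. Randomisation and blinding states: "A covariate-adaptive randomisation procedure for two treatments will be applied to balance the treatment allocations across the selected covariates (sex, age, BMI"). That balancing concerns the two treatments only.

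**When they are seen.** Timeline of the study gives "two sample collection points for each healthy participant: at enrolment (-T1) and baseline" (T0), and reserves T1 for psoriasis participants. The text after Table 2, on visits T0 and T1, says "an oral glucose tolerance test and metabolic rate evaluation will be performed in all participants after an overnight fast". Multi-sugar absorption test says "Before the check-up visits T_0_ and T_1_, all participants will complete the multi-sugar absorption test (SAT"). Biological material plans fasting blood and morning urine at T0 and T1 from each participant.

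**How they are compared.** The Statistical analysis plan says that, for secondary outcomes and cross-sectional comparisons, "two- or three-group comparisons will be performed using a t-test or ANOVA", with Mann–Whitney or Kruskal–Wallis as fallback. Adjustment for sex, age and BMI is stated for the primary PASI model and for PASI50, not for these tests. Strengths, risks and limitations says: "Another strength of this RCT is that it is a prospective study with a comparable healthy subject control group".

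**The concern.** Randomisation protects the prebiotic-versus-placebo contrast. Nothing in the design does the same for psoriasis versus health. The two populations are recruited by different routes, and eligibility ranges as wide as 18–65 years and any BMI below 30 leave room for quite different age, sex and BMI distributions. Several of the measured quantities (glucose tolerance, lipids, body composition, resting metabolic rate) could plausibly vary with those factors. A t-test, ANOVA or rank test would attribute such a difference to disease.

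The visit conflict is a separate, factual problem. It decides whether healthy volunteers attend a second round of procedures, and whether any healthy values exist that are concurrent with the patients' week-8 values.

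**Working it through.** **1. Visit text side by side.**

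| Section | Healthy group at T0 | Healthy group at T1 |
|---|---|---|
| Timeline of the study | yes | no (enrolment and T0 only) |
| Text after Table 2 (glucose tolerance test, metabolic rate) | yes, all participants | yes, all participants |
| Multi-sugar absorption test | yes, all participants | yes, all participants |
| Biological material (blood, urine) | yes, each participant | yes, each participant |

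The article separates the groups where it means to: PASI at enrolment is for psoriasis patients, and the biopsy paragraph treats the two groups separately. The unqualified wording elsewhere is therefore not obviously shorthand for psoriasis patients. Table 2 and the figures are not shown and may agree with one version, but the running text would still conflict.

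**2. Which groups enter a three-group test.** The trial has prebiotic, placebo and healthy groups and no others. A three-group comparison must include the healthy group. The article does not say so; it follows by counting.

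**3. Which covariates enter.** None of the four named tests takes covariates. The plan's general sentence on linear and logistic regression for associations is not assigned to the healthy comparisons. The diet covariates are assigned to sensitivity analyses and microbiome association models.

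**4. Size, as an illustration.** The plan gives no figure to reproduce here: the Sample size section covers the randomised arms only (30 per arm randomised, about 25 evaluable), and no size is stated for the healthy group. Assumptions not in the documents:
- 30 in each of the three groups;
- no true disease or treatment effect;
- the healthy mean shifted by s standard deviations solely through an unadjusted covariate.

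The shift is s = D × r, where D is the covariate imbalance in SD and r its correlation with the outcome. For example, D = 0.5 with r = 0.5 gives s = 0.25, and D = 0.8 with r = 0.5 gives s = 0.40.

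With equal n the grand mean is s/3, so the noncentrality is

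λ = n[(2s/3)² + 2(s/3)²] = n × (2/3)s² = 20s² for n = 30.

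The 5% critical value of F with 2 and 87 degrees of freedom is 3.101. The noncentral-F rejection probabilities are:

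| Shift s | λ = 20s² | Rejection rate at nominal 5% |
|---|---|---|
| 0.10 | 0.20 | 6.5% |
| 0.25 | 1.25 | 15% |
| 0.40 | 3.20 | 33% |

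**5. Sensitivity to group size.** With 25 evaluable per psoriasis arm, the rates at s = 0.25 are 13%, 14% and 19% for 25, 30 and 60 healthy subjects. At s = 0.40 they are 28%, 31% and 44%. With no covariate imbalance, or with correct adjustment, the rate is 5%.

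**The case against.** **The visit conflict may be loose wording.** The Timeline section is the only one that sets visits by group, and it refers to Table 2. Healthy subjects receive no supplement, so a visit defined as following the 8-week intervention has no evident meaning for them. This is a fair argument about what was intended. It does not remove the conflict, because three later sections say otherwise.

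**A reader might infer that week-8 patient values will be tested against healthy T0 values.** The documents do not support this. No section plans a three-group test at T1. Study outcomes defines the secondary outcomes as changes within and between the prebiotic and placebo groups, and a subject without T1 has no such change. The natural reading is that three-group tests are the cross-sectional ones, and T0 is the visit that every version of the text gives to all groups.

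**A reader might infer that the treatment effect will be read from an omnibus ANOVA, whose p-value could be driven by psoriasis versus health.** No section says so. The plan compares the prebiotic group with the placebo group under intention to treat.

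**A reader might say that the comparisons are confounded, and that the group is the benchmark for restored homeostasis.** The documents support only that they are open to confounding: the shared eligibility criteria limit imbalance, and its actual extent is unknown. The Hypothesis section does not mention the healthy group.

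**Covariates for an ancillary group may be left to a fuller analysis plan.** This would hold if the article were silent. It names tests that take no covariates.

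**The figures rest on assumptions.** This is correct; none of the inputs comes from the documents. The choice of procedure also matters. A two-sample t-test of 30 healthy against 60 pooled patients would give about 7%, 20% and 42% for the same shifts. Those rates describe that test, not the three-group ANOVA. They do show that pooling the patients without adjustment would not help.

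**Conclusion.** Two points stand. First, the Timeline section and the three sections after it contradict each other on healthy T1 procedures and must be reconciled. Second, the stated tests leave comparisons with an unmatched, separately recruited group unadjusted for age, sex and BMI, so these comparisons are open to confounding and the claim that the group is comparable is not secured by the design.

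The importance is moderate. The primary PASI analysis and the randomised secondary comparisons are untouched; what is exposed is any statement about how psoriasis patients differ from healthy people. On the illustrative assumptions, the false-positive rate of a nominal 5% three-group ANOVA goes from barely raised (6.5% at 0.1 SD) to a third (33% at 0.4 SD). The true figure depends on an imbalance and a healthy-group size that the documents do not give.

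**What to change.** 1. Reconcile Timeline of the study with the text after Table 2, Multi-sugar absorption test and Biological material, so that each procedure states which groups have it at which visit.
2. In the Statistical analysis plan, compare healthy subjects with all psoriasis patients pooled at T0, before any supplement, in a linear model adjusted for age, sex and BMI. This addresses those three factors only; differences tied to the recruitment route may remain and should be acknowledged.
3. State that three-group tests are not used for treatment effects, which stay in the two-arm comparison.
4. If any T1 comparison with healthy subjects is made, name the healthy visit that supplies the reference values and label the comparison descriptive.
5. Drop or qualify the word comparable in Strengths, risks and limitations.

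The cost is wording and a regression in place of ANOVA. Age, sex and BMI are already collected, and neither recruitment nor the randomised comparison changes.

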**Table 2 Tab2:**
[figure not shown]
Schedule of enrolment, intervention and assessments [24]

During the enrolment visit (-T_1_), vitals (systolic, diastolic and pulse pressure), body height (stadiometer Seca 213, Seca GmbH & Co, Hamburg, Germany), and body weight (balance Seca 813 Med, Seca GMBH & Co, Hamburg, Germany) were measured in all participants. The body mass index (BMI) was calculated as a ratio of body mass to the square of body height and expressed in kg/m^2^. In addition, a qualified nurse collected a sample (8 mL) of venous blood into a serum vacuum tube (Greiner Bio-One GmbH, Kremsmünster, Austria) to perform a serum IgA antibody against tissue transglutaminase (anti-tTG IgA) assay to rule out gluten-related diseases (e.g., celiac disease) [30]. A dermatologist assessed the severity of skin lesions in PS patients using the Psoriasis Area and Severity Index (PASI).

During the check-up visits T_0_ and T_1_, vitals, anthropometric indices, and body composition will be measured, and an oral glucose tolerance test and metabolic rate evaluation will be performed in all participants after an overnight fast. Additionally, surveys on nutritional status and quality of life will be conducted, and samples of biological materials (blood, urine, urine after SAT, stool, skin) will be collected.

### Multi-sugar absorption test

Before the check-up visits T_0_ and T_1_, all participants will complete the multi-sugar absorption test (SAT) [31]. They will be instructed to perform the test on a day off from work, one day before the scheduled check-up visits. Participants will be asked to follow pre-test restrictions: maintaining normal daily activities and typical dietary patterns, but 2 days before the test, avoiding consumption of sugars (sucrose, lactulose, sucralose, erythritol and rhamnose) present in the sugar mixture, as well as alcohol, caffeine, and spicy foods.

On the test day, after an overnight fast and morning bladder emptying, subjects will ingest a sugar mixture (containing 1 g sucrose (PA-01-0238-O, POL-AURA, Morąg, Poland), 1 g lactulose (PA-03-9831-C, POL-AURA, Poland), 1 g sucralose (PA-03-9213-C, POL-AURA, Poland), 1 g erythritol (E968, Hortimex Plus Sp. z o.o. Sp. K,. Konin, Poland) and 0.5 g L-rhamnose (PA-03-1712-C, POL-AURA, Poland)), freshly dissolved in 150 mL of tap water. They will then be instructed to collect urine in a tulip-type container over 12 h. During the test, they will be permitted to drink water (150–200 mL per hour) to maintain adequate urinary output, but will not be allowed to eat for the first 5 h. Participants will collect urine samples at three intervals: 2, 5, and 12 h after ingesting the sugar mixture, and record the urine volume at each interval.

